1    **Effects of immersive virtual reality intervention on pain and anxiety among pediatric**  
2    **patients undergoing venipuncture: A randomized controlled trial**

4    ***Lead PI:** [name] [name], Assistant Professor, the Nethersole School of Nursing, Faculty*  
5    *of Medicine, the Chinese University of Hong Kong*

6    ***Site PI:** [name], Ward Manager, Department of Paediatrics and Adolescent*  
7    *Medicine, Tseung Kwan O Hospital*

9    **Abstract**

10    Venipuncture is one of the most painful and distressing procedure experienced by  
11    pediatric patients. Unmanaged pain has short- and long-term consequences to patients.  
12    Moreover, it prolongs the procedure and consumes additional manpower while decreasing the  
13    satisfaction of health-care providers. Evidence suggests that distraction combined with age-  
14    appropriate procedural information can effectively decrease procedural pain and anxiety in  
15    pediatric patients. This integrated approach, however, may be difficult to implement and  
16    consumes high amounts of manpower and time.

17    Immersive virtual reality (IVR) has become possible with technological advancement. It  
18    can simultaneously provide complete distraction and procedural information to patients.  
19    However, its effects on pediatric patients undergoing venipuncture are unknown.

20    Guided by the Gate Control Theory and the Lazarus and Folkman's Theory, this study  
21    aims to examine the effects of IVR intervention on reducing the pain, anxiety and stress  
22    experienced by pediatric patients undergoing venipuncture. It will also examine the effects of  
23    IVR on the duration of venipuncture and the satisfaction of health-care providers for the  
24    procedure. Its cost-effectiveness will also be evaluated. A randomized controlled trial with  
25    repeated assessments will be conducted. A total of 250 pediatric patients aged 4–12 years will

26 be recruited from a regional public hospital and randomly assigned to either the intervention  
27 or control group. The study will use two age-appropriate IVR modules that consist of  
28 procedural information developed by the lead principal investigator. The intervention group  
29 will receive IVR intervention, whereas the control group will receive standard care only. 10  
30 health-care providers involved in the venipuncture procedure will also be invited to  
31 participate to assess their satisfaction level towards the procedure. The primary outcome is  
32 child-reported pain. Secondary outcomes include child-reported anxiety, heart rate, salivary  
33 cortisol, length of procedure, and satisfaction of health care providers with respect to the  
34 venipuncture procedure. The cost-effectiveness of IVR intervention will be compared with  
35 that of standard care. Outcome evaluation will be conducted at four time points: 10 minutes  
36 before, during, and immediately after and 30 minutes after the procedure. Intention to treat  
37 and generalized estimating equation model will be used to analyze the data.

38 This study is the first of its kind to adopt IVR intervention with age-appropriate  
39 procedural information for pediatric patients undergoing venipuncture. Findings of the  
40 proposed study may (1) provide a novel, facile, and cost-effective intervention that can be  
41 used virtually at any time and place to manage pain and anxiety; and (2) shed light on the  
42 global trends of research and clinical development of IVR as an intervention for other painful  
43 and stressful medical procedures.

44

45

46

47

48

49

50

## 51    **Background of research**

52       Hospitalized children experience pain and anxiety from invasive procedures and/or their  
53    underlying diseases [1]. Venipuncture, a frequently performed needle-related procedure, is  
54    the most frightening experience and a common source of moderate to severe pain for  
55    pediatric patients [1-2]. The pain associated with the procedure is secondary only to the  
56    illness itself [3]. Approximately 83% of children aged 2.5–6 years, 51% of children aged 7–  
57    12 years, and 28% of adolescents (>12 years of age) who underwent venipuncture reported  
58    high levels of distress during the procedure [4]. However, less than 10% of venipuncture  
59    procedures are provided with pain management [2].

60       Inadequate pain management can negatively affect children, parents, and medical  
61    institutions [5-10]. Unmanaged needle-related procedural pain in children is associated with  
62    increased pain and stress during subsequent procedures, fear and avoidance of medical care,  
63    or even the development of needle phobias that persist into adulthood [3, 6-8]. Failure to  
64    manage needle-related pain may increase the manpower, resources, and time required to  
65    complete procedures, consequently reducing health-care providers' satisfaction with respect  
66    to the procedures [5, 10].

67       Pre-procedural local analgesics have been traditionally used to manage needle-related  
68    procedural pain. However, high levels of pain and distress were reported in children even  
69    with pharmacological interventions [11-12]. Thus, clinical guidelines highlight the important  
70    role of non-pharmacological interventions alone or as clinical adjunct in managing procedural  
71    pain [13].

## 72    **Non-pharmacological interventions**

73       Various studies have suggested non-pharmacological interventions, such as distraction,  
74    procedural information provision, hypnosis, and cognitive behavioral therapy, to manage the  
75    pain and anxiety experienced by pediatric patients undergoing needle-related procedures [14-

16]. However, distraction and information provision are more feasible to implement than previously suggested interventions because many clinicians are not trained in hypnosis or cognitive behavioral therapy.

Distraction is the most effective non-pharmacological intervention for mitigating the pain and anxiety experienced by pediatric patient undergoing needle-related procedures [14-16], particularly in children aged below 12 years [16]. A review of 26 studies involving 2,548 children aged 2–19 years showed that needle-related procedures have been performed with various distractors, such as listening to music; watching cartoons; playing with toys; and mother-directed distractions, like soothing [14]. However, further research is needed to identify the most efficacious type of distractor [16]. Nevertheless, the review suggested that distractions without adult involvement (supportive role articulated for the adult within the intervention) and child choice effectively reduce the intensity of self-reported distress [14]. In addition, developmentally age-appropriate distractors for children are important for successful pain management [16-17]. Two recent studies further confirmed that distraction intervention integrated with procedural information produce significant outcomes [18-19]. However, simultaneously providing age-appropriate distraction and procedural information may be difficult and may likely increase the workload of hospital staff. Most importantly, previously employed distractors (e.g. music, cartoon, or toys) failed to provide complete distraction because children still inevitably see the needles, which is the most distress-evoking experience in needle-related procedures [5-6]. Thus, intervention that can provide age-appropriate procedural information and completely distract the attention of children from painful stimuli should be identified.

## **Immersive Virtual Reality**

Immersive virtual reality (IVR) may help overcome the above obstacles. It provides a means of human/computer interaction, wherein a human becomes an active participant in a

virtual environment created through a head-mounted display [20]. The user is immersed and actively participates in the virtual environment as it changes in real time with the user's movements [21]. Moreover, it can be used at any time and place in clinical settings without requiring extra manpower. Thus, it can be easily provided as an intervention for patients. IVR modules can also be tailored to provide health information to the user. The cost of IVR equipment has also become increasingly affordable. For instance, the price of a commercially available disposable IVR headset (VR Goggles) is only about HK \$15. Distraction-based IVR intervention has already been implemented in the Lucile Packard Children's Hospital at Stanford in the United States [22].

#### **Studies of the Effects of IVR on Procedural Pain and Anxiety**

A large body of evidence supports the efficacy of IVR in reducing pain, anxiety, and stress among pediatric patients undergoing burn care or cancer treatments [20-21]. With regard to needle-related procedures, a randomized control trial was conducted with 20 pediatric patients aged 8–12 years and who required peripheral intravenous access [11]. The intervention group received IVR prior to the procedure, whereas the control group received local anesthetic spray without IVR. Pain was measured using the Faces Pain Scale-Revised (FPS-R). Participants in the intervention group reported that their perceived pain was not significantly different, whereas those in the control group reported a four-fold increase in pain following the procedure [11]. Two studies involved pediatric oncology patients aged between 7–19 years and who were undergoing port access (insertion of a needle into an implanted device to facilitate blood collection or injections). Participants in the intervention group were immersed in a virtual gorilla habitat. Results found that the heart rates of participants in the intervention group significantly decreased, indicating that children in the intervention group did not experience as much pain and anxiety as those in the control group [23-24]. Another study on children with cancer (aged 5–18 years) undergoing venipuncture

( $n = 4$ ) or port access ( $n = 46$ ) allowed patients in the intervention group to select from various immersive and non-immersive distractors (such as books, IVR, music, and video games) [25]. The self-reported pain of patients in the IVR group was no different. However, a reduction of fear and distress was reported by the outcome assessors in IVR group.

The research team led by the lead principal investigator (lead PI) is conducting a pilot trial on the feasibility and acceptability of IVR as a distraction intervention for pediatric oncology patients undergoing needle-related procedures. Preliminary results suggested that IVR is feasible and is acceptable to children, parents, and health care providers in Hong Kong. Patients in the intervention group reported reduction in pain and anxiety score after IVR.

Although previous studies have provided some positive findings regarding the effects of IVR on needle-related procedural pain and anxiety, these studies involved small sample sizes ( $n = 20$  to 59) [11, 23-25] and recruited children of various developmental ages (5–19 years) without using age-appropriate IVR modules [11, 23-25]. Most importantly, all these studies adopted IVR as a distraction intervention only. To our knowledge, no study has utilized IVR to provide distraction and procedural information to patients undergoing venipuncture. Given that venipuncture is the most painful and fearful procedure for pediatric patients [1-4], future large-scale studies on the efficacy of IVR to provide complete distraction and procedural information to pediatric patients undergoing venipuncture may offer crucial insight on the application of this approach. The satisfaction of health care providers and the cost-effectiveness of IVR intervention should also be examined to aid decisions for the application of this approach in routine clinical practice.

## **Theoretical Frameworks**

The Gate Control Theory and Lazarus and Folkman's theory provide the theoretical underpinning of this study [26-27]. The gate control theory suggests that peripheral nerves

become excited when cells are damaged. Impulses from nerves pass along to spinal cord systems and other neuroanatomical structures before reaching the cerebral cortex where pain is perceived. The gate control system in the spinal cord opens and closes to modulate pain perception. If non-nociceptive input (IVR) exceeds the nociceptive (pain) input, then the gate can partially or entirely close, blocking the transmission of the pain signal to the brain. The theory also proposes that pain signals that descend from the brain through the gate can be amplified by emotional experiences, such as anxiety and stress. Lazarus and Folkman's theory [27] states that an individual's evaluations of anxiety and stress-provoking experiences are influenced by their perceptions of control over a potential threat. Providing information may help improve pediatric patients' sense of control over a procedure [18-19, 28].

In the context of these two theories, IVR functions by providing multisensory input to divert the children's conscious attention from venipuncture-associated pain, thus helping close gate control and decreasing pain perception [29]. The analgesic effects of IVR have been supported by the results of functional magnetic resonance imaging assessment [30]. Providing procedural information through IVR modules further help increases the children's sense of control over the procedure, thereby reducing their stress and anxiety, as well as pain signals transmitted through the gate control system. Therefore, IVR intervention will likely reduce pain, anxiety and stress; these changes are evidenced by physiological changes in the heart rates and salivary cortisol levels of the patients. Thus, patients may show increased procedural compliance, consequently decreasing the length and cost of the procedure while possibly improving the satisfaction of the health-care providers with the procedure [5, 10].

## **Aim**

This study aims to examine the effects of IVR intervention on reducing pain, anxiety, stress, and length of procedure among pediatric patients undergoing venipuncture. The satisfaction ratings of health care providers toward the procedures and the cost effectiveness

of the IVR intervention will also be evaluated.

### **Hypotheses for testing:**

- (1) Compared with standard care, IVR intervention significantly reduces pain, anxiety, stress, and length of procedure in pediatric patients undergoing venipuncture;
- (2) Compared with standard care, IVR intervention significantly improves the satisfaction of health care providers toward the venipuncture procedures;
- (3) IVR intervention is significantly more cost-effective than standard care for pediatric patients undergoing venipuncture.

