**Length of procedure:** A standard stop watch will be used to measure the length of the procedure from the beginning (time when the doctor/phlebotomist starts to disinfect the site) to the end of procedure (time when applies the band aid on the venipuncture site).

**Staff satisfaction scale:** The staff satisfaction scale will be adopted to measure the satisfaction levels of the health care providers toward the procedure [45]. It consists of 8-item and each rated by a 5-point scale ranging from 1 = strongly disagree to 5 = strongly agree. Higher score presents a higher level of the satisfaction. This scale has been translated by the PI using back-translation method recommended by Brislin (1970) and used in a previous study with the Cronbach's alpha of 0.90 [41].

**Cost-effectiveness:** Cost analysis will be examined based on incremental cost-effectiveness ratio expressed as incremental cost per every one unit decrease in the primary outcome of the FPS-R scale immediately post-intervention with respect to the baseline. All the cost data involved will be expressed in Hong Kong dollars and valued on the starting date of the study on the basis of non-subsidized cost. All costs incurred will be estimated per each participant using the method of Thompson & Barber [46]. Specifically, the cost of human resources (e.g. doctors, nurses, phlebotomist, and health care assistants) is measured by the salary of the middle rank of the professionals and calculated based on the minutes used to perform the procedures. Costs of consumables to perform the venipuncture (e.g. alcohol pad, glove, butterfly needles, and band aid) will be based on the retail price paid by the finance office of the hospital. In addition, the cost for development of IVR modules and VR goggles will be included in the intervention group.

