## **Data analysis**

IBM SPSS 24 will be used for data analysis. Continuous demographic and clinical variables will be presented as their means and standard deviations, whereas categorical data (e.g. sex) will be presented in frequencies and percentages, as appropriate. The intention-to-treat principle will be adopted for the outcome comparisons between the intervention and control groups. The generalized estimating equations (GEE) model will be used to compare each of the outcome measures across the time points between the two groups. GEE model can account for intra-correlated repeated measures data and produce unbiased estimates even if there are missing data, provided that the data are missing at completely random. Cohen's d values will be calculated to estimate the effect sizes of the IVR intervention on the outcome variables. All statistical analyses are two-sided and level of significance will be set at 0.05.

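### Hypothesis 3 promises a significance verdict on cost-effectiveness, but the only measure fixed is an ICER with no decision rule, and the only named model cannot test it

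*Protocol*

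**What the plan says.** Under Hypotheses for testing, the third hypothesis of the Protocol is that "IVR intervention is significantly more cost-effective than standard care for pediatric patients undergoing venipuncture".

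The Cost-effectiveness paragraph under Secondary outcomes bases the cost analysis on an "incremental cost-effectiveness ratio expressed as incremental cost per every one unit decrease in the primary outcome of the FPS-R scale", taken immediately after the intervention relative to baseline. For the inputs it says: "All costs incurred will be estimated per each participant using the method of" a cited paper on cost data in trials. It then adds: "In addition, the cost for development of IVR modules and VR goggles will be included in the intervention group".

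Data analysis names GEE for comparing each outcome measure across the time points between the groups, and closes: "All statistical analyses are two-sided and level of significance will be set at 0.05".

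On direction, Theoretical Frameworks expects that "IVR intervention will likely reduce pain, anxiety and stress". It suggests that children may comply better, "consequently decreasing the length and cost of the procedure".

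The Protocol gives no value per FPS-R point, no net-benefit measure, no interval for the ICER and no rule for calling one arm more cost-effective. No statistical analysis plan was available.

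**The concern.** A hypothesis worded as a significance claim needs a statistic with a null value and a test. The Protocol supplies neither for hypothesis 3.

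- **No null value.** An ICER of, say, HK$50 per point means neither cost-effective nor not cost-effective until someone says what a point is worth.
- **No applicable model.** GEE compares repeated measurements on children. The ICER exists once per trial, as the between-arm cost difference over the between-arm effect difference.
- **Ambiguous sign.** A given ICER, positive or negative, can come from two results with opposite meanings.

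Cost-effectiveness is one of three hypotheses and part of the stated aim. Run as written, the same data could be reported as significantly cost-effective or not, depending on a price chosen after the results are seen. Alternatively, significance could be borrowed from the pain comparison alone.

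**Working it through.** **1. The protocol's own figure.** Sample size – Patients gives a difference of 0.8, SD 1.84, 80% power and 5% two-sided.
- Normal approximation: n = 2 × (1.960 + 0.842)² × (1.84/0.8)² ≈ 83.04, rounded up to 84 per group.
- t-test version: 84.01, rounded up to 85.
- 170/0.85 = 200 and 200/0.80 = 250.

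The stated 85, 200 and 250 reproduce and are not at issue. They rest on FPS-R only; nothing is sized for cost-effectiveness.

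**2. Definitions.** Let dC be the cost of IVR minus standard care, dE the extra FPS-R reduction with IVR, and L the value in HK$ of one FPS-R point.
- ICER = dC/dE.
- Incremental net monetary benefit INB(L) = L × dE − dC.
- With n per arm and cost and effect uncorrelated, SE = √[(2/n) × (SD_cost² + (1.84 L)²)].

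**3. What the ICER shows by sign** (illustrative pairs)

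| dC (HK$) | dE (points) | ICER | Meaning |
|---|---|---|---|
| +20 | +0.8 | 25 | dearer, better |
| −20 | −0.8 | 25 | cheaper, worse |
| −20 | +0.8 | −25 | cheaper, better |
| +20 | −0.8 | −25 | dearer, worse |
| −20 | +1.6 | −12.5 | cheaper, better by more |
| −40 | +1.6 | −25 | better still on cost |

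Among the three cheaper-and-better results, the size of the ratio does not rank them. The value −25 is shared with the worst outcome.

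**4. Is the sign of dC predicted?** Only the cost of the procedure is expected to fall, and tentatively. The IVR arm also carries goggles at about HK$15 (Immersive Virtual Reality section) and module development. The development cost D is not given. Spread over 125 children, the add-on is D/125 + 15:
- D = 0: HK$15
- D = 10,000: HK$95
- D = 50,000: HK$415
- D = 100,000: HK$815

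The net sign is therefore open.

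**5. If IVR is dearer and better, the price decides.** dE = 0.8 and SD 1.84 come from the Protocol. The cost inputs and L are assumptions. I use 85 per arm (the planned evaluable number) and 106 per arm (250 × 0.85/2 = 106.25, attrition only).

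*Assumed dC = +40, SD_cost = 100 (ICER = 40/0.8 = 50):*

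| L | INB | p, n = 85 | p, n = 106 |
|---|---|---|---|
| 0 | −40 | 0.009 (against IVR) | 0.004 (against IVR) |
| 50 | 0 | 1.00 | 1.00 |
| 100 | +40 | 0.21 | 0.16 |
| 200 | +120 | 0.040 (for IVR) | 0.022 (for IVR) |

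Check at L = 200, n = 85: SE = √[(2/85)(100² + 368²)] = 58.5, and 120/58.5 = 2.05.

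*Assumed dC = +100, SD_cost = 60 (ICER = 100/0.8 = 125). Probability that IVR is cost-effective = Φ(INB/SE):*

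| L | n = 85 | n = 106 |
|---|---|---|
| 100 | 25% | 23% |
| 125 | 50% | 50% |
| 200 | 85% | 88% |
| 300 | 95% | 97% |

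In this second scenario, L = 300 gives p = 0.10 at 85 per arm (140/85.2 = 1.64) and p = 0.07 at 106 (140/76.3 = 1.84).

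**6. If IVR is cheaper and better, no price is needed.** With dC = −40, SD_cost = 100 and n = 85, INB favours IVR at every L tried from 0 to 400, with p between 0.0001 and 0.009. Dominance is visible from the two differences or from INB. The ICER is −50, which by itself could equally be dC = +40 with dE = −0.8.

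**The case against.** The strongest reply is that a value range, an interval method, an acceptability curve and dominance reporting commonly belong in an analysis plan, which is not at hand. The Protocol bases the analysis on an ICER without calling it the only statistic, and net benefit uses the same cost and effect data. It also cites a paper on analysing trial cost data, and nothing can be inferred here about what that paper prescribes. This stands as far as the details go: their absence alone is no finding. It does not remove the conflict in the current text. A significance claim is paired with a measure that cannot carry one, and a later plan would have to add a decision measure or reword the hypothesis.

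A reader might infer two stronger things, and the Protocol supports neither.

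- **That hypothesis 3 cannot be tested at all.** If IVR is both cheaper and less painful it dominates at every non-negative price, and the two differences can each be tested at two-sided 0.05. The missing price matters only when cost and effect pull in opposite directions.
- **That the ratio fails in the very case the Protocol predicts.** The text on falling cost is tentative and covers the procedure only, while development and goggles are charged to IVR. Net cost may be positive, and with a pain benefit the ICER is then readable as a price per point.

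It is also fair that the illustrations depend on assumed costs, and that the ratio misleads only if the two differences are not shown. The Protocol does not say they will be hidden, nor that they will be shown.

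**Conclusion.** The point holds as a mismatch between the wording of hypothesis 3 and the measure and model the Protocol fixes. Both favourable outcomes are affected, for different reasons. If IVR is dearer and better, the verdict turns on an unstated value per FPS-R point. If it is cheaper and better, the conclusion is sound at any value, but the ICER does not show it.

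The size is illustrative only. It rests on assumed cost differences and SDs, uncorrelated cost and effect, a normal approximation, and the Protocol's 0.8 and 1.84. With IVR HK$40 dearer, the verdict moves from significantly against to significantly for IVR as the value goes from HK$0 to HK$200 per point. With IVR HK$100 dearer, the probability of cost-effectiveness goes from about 25% to 95% between HK$100 and HK$300. The pattern is the same at 85 and 106 per arm.

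This is a secondary objective. It should be corrected, but it leaves the primary FPS-R analysis and the sample size untouched.

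**What to change.** - **Hypotheses for testing, item 3:** restate as estimation of the cost-effectiveness of IVR relative to standard care, and drop the word *significantly*.
- **Secondary outcomes, Cost-effectiveness:** report the cost difference and the FPS-R difference separately, with 95% confidence intervals from a bootstrap that resamples children so that each child's cost and effect stay together.
- **Decision measure:** use incremental net monetary benefit over a range of values per FPS-R point stated in advance, shown as an acceptability curve.
- **Reporting rule:** state dominance when IVR is both cheaper and better, and give the ICER only when both differences are positive.

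The cost is a change of wording in two places and a short analysis of data already planned; no new data are needed. What is lost is a single headline of significantly greater cost-effectiveness, because net benefit over a range gives a curve and not one verdict.
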